#### Economic evaluation

*Cost data* will be obtained weekly during the parenting class for participants in arm 3 and during weekly compliance checks for participants in arms 2 and 3. For economic evaluation, research-only costs are excluded. We will measure the incremental costs of the egg (arm 2) and egg + parenting (arm 3) interventions compared to usual care (arm 1) by building participant-level cost items on time, transportation, and indirect costs into the baseline and quarterly data collection points and by measuring other intervention costs. Participants in both intervention arms may incur costs from additional time spent preparing or feeding eggs. Additionally, participants in the *Grandi Byen* arm may incur costs for time spent in the 10 sessions and for transportation. Costs to purchase, store, and deliver eggs apply to arms 2 & 3. Arm 3 also includes costs of materials, facilities for conducting the 10 sessions (community sites have an opportunity cost, even if they are provided gratis), and facilitators (for administering the intervention, 3 days of training, and transportation). Opportunity costs [88], which may differ from budgetary costs, will be measured to facilitate a social perspective.

### Statistical analyses

#### Primary and secondary outcomes

Inferential tests will be applied in the analyses for this trial. To determine differences across the three study arms, all analyses will follow an intention-to-treat framework. Moreover, all hypothesis testing will be based on a one-sided superiority paradigm because the analyses will examine whether the study interventions have beneficial impacts for the children in the study. A one-sided superiority framework is therefore legitimate, because by the theory of change for the development of the treatment program, the intervention’s positive impacts are predictable, and efforts will be made to minimize any unintended and undesirable side-effects. Specifically, the hypothesized sign for outcome variables has a positive sign, except for the child morbidities and infection, which we hypothesize to be reduced, thus indicated by a negative sign for the coefficient.

Descriptive statistics will be used to detail baseline socio-economic, demographic, and household characteristics of the study sample. Additionally, baseline and endline characteristics for the outcomes of interest will be presented in a table with means and standard deviations or medians with interquartile ranges for continuous variables and as percentages for categorical variables. Several variables represented in summary statistics will also be used as covariates in adjusted outcome analyses to ensure a convincible level of internal validity for key study variables such as the treatment effects. Additionally, covariates will be included in analyses based on the hypothesized pathways in Fig. 2 and will also be derived empirically. Empirically derived covariates will be included in analyses when a p-value < .1 results from the likelihood ratio test or the Wald test.

The primary analytic model to test primary hypotheses of the primary study aims—aims 1 and 2 (Table 1)—is the growth curve analysis using hierarchical linear modeling (HLM) or hierarchical generalized linear modeling (HGLM), depending on whether the outcome variable is a normally distributed continuous variable or a categorical variable. In the current study, the different timepoints (i.e., five waves of data collection at baseline and 3-, 6-, 9-, and 12-month follow-ups) are nested within children. These clustering effects violate the independent-observation assumption embedded in a linear model, so we will use HLM (also known as a random-effect or mixed-effect model) to control for the nesting structure of the data. In this study sample, there is only one child per parent, thus the nesting effect of children within families is absent. We therefore plan to treat mother-child pairs as one study level. However, we apply a two-level HLM model that treats time as level 1 and children as level 2.

Aim 3 examines the pathways to child growth and development by testing a series of mediational effects of secondary outcomes: responsive parenting, child dietary diversity and nutrient intakes, biomarker status, allergies, bone maturation, acute diarrhea, and respiratory morbidity. To conduct HLM or HGLM analysis for this aim, we will employ the multilevel analysis specially developed for testing mediational effects [89]. The analysis will involve three models: a full model, a reduced model, and a model using the mediator as a dependent variable. For the time-to-event outcomes (diarrhea episode, respiratory infections, and allergies in first 6 months of follow-up), we will use a proportional hazards model [90, 91].

To prevent data missingness, the field study coordinator will review the data to ensure data completeness prior to weekly data uploads to the secure Research Electronic Data Capture (REDCap) server hosted at Washington University in St. Louis [92]. The coordinator will subsequently follow up with study enumerators responsible for entering a given participant’s data to address quality issues and facilitate follow up with the study participant. Additionally, prior to all data analysis, presence, type, and number of missing observations will be explored. Logistic regression models will determine the type of missingness, whether data are missing at random (MAR), and whether the missingness is monotonic or non-monotonic. To address the possible issues with missing data, multiple imputation techniques [93] will be used to secure robust and unbiased results. Multiple imputation is highly recommended when data are MAR or missing completely at random MCAR [94, 95]. A minimum of 20 imputed files will be generated by using chained equations at the imputation stage. Outcome analysis will be performed on each imputed file, and results are aggregated by applying Rubin’s rule [93].

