Disentangling which specific elements (psychosocial or hygiene and sanitation practices) of the intervention did most to enhance the nutrition intervention may be useful for future adaptations to other contexts. However, our emphasis will be on the effects of the bundled intervention, which is a common practice in medical research [58, 59]. In aim 3, we will explore hypothesized pathways from the interventions to growth and development impacts (Fig. 2). The *Grandi Byen* intervention is anticipated to influence parenting practices through improvements in caregiving and child stimulation, household environmental conditions for WASH, and child feeding for dietary diversity and ASF consumption, which may in turn reduce infectious disease incidence, improve bone maturation, and increase blood concentrations of critical nutrients. By contrast, the egg intervention alone may affect nutrition biomarkers, infection, or bone maturation to a lesser extent but is unlikely to strongly influence child development outcomes. Finally, children in the standard well-baby care group should show little or no impacts on growth and development.

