**Fig. 2 Fig2:**
[figure not shown]
Hypothesized pathways from study conditions to outcomes

The fourth aim highlights a major gap related to the effective translation and continuity of evidence-based programs in real-world settings by addressing economic considerations related to public health programming. We intentionally selected interventions (egg only and *Grandi Byen*) that are feasible for translation into programming and policy with preliminary evidence to support this [60]. Experts in implementation science recognize that there is limited research on cost-effectiveness of evidence-based interventions and emphasize that future research addresses this gap [61]. Multicomponent interventions are at risk for being expensive and complicated to reproduce in multiple contexts [62]. Moreover, costly interventions would likely not be sustainable in low-resource contexts [63]. The inclusion of an economic evaluation will allow us to determine whether any incremental benefits associated with *Grandi Byen* when compared to an egg-only intervention and standard well-baby care are favorable relative to additional costs, a question of efficiency. Given that millions of children globally living in poverty are not reaching their full developmental potential, there is a tremendous need for efficacious and cost-effective interventions to disrupt early childhood trajectories towards long-term deleterious outcomes.

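### The covariate rules are not limited to baseline variables or to Aim 3, so as written they permit adjusting the Aims 1 and 2 effects for the interventions' own mediators

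*Protocol article*

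**What the plan says.** The Statistical analyses section of the Protocol article, under Primary and secondary outcomes, gives covariates three sources.

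- Descriptive tables: some summarised variables are to be "used as covariates in adjusted outcome analyses to ensure a convincible level of internal validity for key study variables such as the treatment effects". The tables cover baseline socio-economic, demographic and household variables, but also "baseline and endline characteristics for the outcomes of interest will be presented in a table".
- Theory: "covariates will be included in analyses based on the hypothesized pathways in Fig. 2 and will also be derived empirically".
- Data: "Empirically derived covariates will be included in analyses when a p-value < .1 results from the likelihood ratio test or the Wald test".

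The caption of Fig. 2 is "Hypothesized pathways from study conditions to outcomes". The section on study aims and hypothesized pathways introduces the figure in connection with Aim 3. It says the multicomponent arm should change parenting practices, household WASH conditions and child feeding, "which may in turn reduce infectious disease incidence, improve bone maturation, and increase blood concentrations of critical nutrients". The Study measures section describes the secondary outcomes as presumed mediators of the effect on the primary outcomes.

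Aims 1 and 2 are tested with a two-level growth-curve model (waves within children), for which no separate covariate rule is given. Aim 3 has its own mediation models. All analyses are to follow intention to treat.

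**The concern.** Hypotheses 1 to 4 compare randomised arms, so each concerns a total effect: everything the assigned intervention does, by whatever route. A variable that the intervention changes, and that in turn affects growth or development, carries part of that effect. Putting it in the outcome model removes that part. It also brings in any unmeasured common cause of mediator and outcome, against which randomisation gives no protection. A covariate rule that points to the pathway diagram, without saying baseline only or Aim 3 only, leaves this open for the primary hypotheses.

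The p < .1 rule raises a second, smaller problem that remains even if every candidate is a baseline variable. The adjusted model is then chosen by looking at the outcome data, and it may differ from one endpoint to the next.

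**Working it through.** The protocol gives no figure for this rule, so there is none to reproduce. The check sets the passages side by side and then sizes the consequence under stated assumptions.

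**1. Which models the rule covers.** It stands under the heading for all primary and secondary outcomes, and the stated purpose of adjustment is the validity of the treatment effects. The paragraph on the Aims 1 and 2 growth-curve model follows and adds no restriction. The rule therefore reaches those models unless something excludes them, and nothing does.

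**2. What the rule draws on.** By the caption of Fig. 2 and the text on hypothesized pathways, the pathways run from study arm to outcome through variables that the arms are expected to change.

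**3. Whether such variables could enter in practice.** By Table 3, ASQ is measured at baseline, 6 and 12 months. Responsive parenting, the 24-hour recall and bone age share those visits. The food frequency questionnaire shares all five LAZ waves. Nutrient biomarkers are taken only at baseline and 6 months. Several pathway variables could thus be time-varying covariates; others fit a five-wave model poorly.

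**4. Size of the mediated loss.** Total effect = direct + indirect. With a share m mediated, adjustment leaves (1 − m) × total. Inputs from Table 1: 0.30 LAZ (Hypothesis 1), 0.10 LAZ (Hypothesis 3), effect size 0.36 on cognition (Hypothesis 4). The shares m are assumptions. Power is shown for Hypothesis 1 only, as Φ(δ√(n/2) − 1.645), with n = 200 per arm from the protocol and assumed SD 1, one-sided alpha 0.05 (the level is not stated) and a single follow-up contrast. Here √(200/2) = 10.

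| m | 0.30 × (1 − m) | Power, H1 | 0.10 × (1 − m) | 0.36 × (1 − m) |
|---|---|---|---|---|
| 0 | 0.300 | Φ(1.355) = 0.91 | 0.100 | 0.36 |
| 25% | 0.225 | Φ(0.605) = 0.73 | 0.075 | 0.27 |
| 50% | 0.150 | Φ(−0.145) = 0.44 | 0.050 | 0.18 |
| 75% | 0.075 | Φ(−0.895) = 0.19 | 0.025 | 0.09 |

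**5. Confounding of mediator and outcome.** Let the arm shift the mediator by a = 0.5 SD, let the mediator act on the outcome with slope b = 0.3, and let the direct effect be c = 0.15. The total is 0.15 + 0.5 × 0.3 = 0.30. If an unmeasured factor loads u on the mediator and k on the outcome, the adjusted arm effect is c − a·u·k.

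- u = k = 0.4: 0.15 − 0.5 × 0.16 = 0.07.
- u = 0.4, k = −0.4: 0.15 + 0.08 = 0.23.

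The bias around the direct effect can therefore go either way. A simulation of 2,000 replicates agrees. Without confounding, the unadjusted mean was 0.297 (rejection rate 0.91) and the adjusted mean 0.147 (0.43). With u = k = 0.4 the adjusted mean was 0.072.

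**6. Whether p < .1 screens mediators out.** It does not. In all four simulated scenarios the mediator met p < .1 in essentially every replicate. This assumes that the mediator is a candidate, so it shows only that the threshold is no safeguard.

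**7. p < .1 with baseline candidates.** Table 3 lists eight primary indicators (LAZ, WAZ, WLZ and five ASQ domains), so selection by outcome could produce up to eight covariate sets.

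**The case against.** The strongest reply is that the text is loose but the intention is sound. Fig. 2 is tied to Aim 3 where it is introduced. The covariate sentence speaks of analyses in general, not of the Aims 1 and 2 models. The Aim 3 plan compares a full with a reduced model, which suggests that the authors distinguish effects with and without mediators. The paragraph opens with baseline characteristics, and internal validity is usual language for baseline adjustment. The article does not say that the adjusted model is the primary one. Fig. 2 cannot be inspected and may also hold background variables.

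Much of this stands, and it rules out several stronger readings that a reader might infer:

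- That the trial will adjust its Aims 1 and 2 effects for mediators. The text permits this but nowhere states it.
- That endline values will serve as covariates because they are in the summary table. The article says only that several summarised variables will be used.
- That covariates will differ between arm contrasts. No separate model per contrast is described; only variation by endpoint is possible.
- That both interventions will necessarily be under-reported. Loss of the mediated share pulls towards zero when direct and indirect effects have the same sign, but confounding can act in either direction. The article also expects eggs alone to move several pathway variables less, so the mediated share may differ by hypothesis.

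The reply does not supply the missing restriction. A baseline-only or Aim-3-only reading is possible but unwritten. Nor is this a detail simply left to an analysis plan, since the article states the rules itself.

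**Conclusion.** The concern holds as a defect in a stated rule, with moderate confidence. As written, the covariate rules allow the total randomised effects in Hypotheses 1 to 4 to be adjusted for post-randomisation mediators, and the p < .1 threshold would not prevent it. Separately, p < .1 selection makes any adjusted model depend on the outcome data, even with baseline candidates only.

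The size depends on the mediated share, which the protocol does not give. At an assumed 50%, Hypothesis 1's 0.30 LAZ would be estimated as 0.15, before any confounding bias. If the unadjusted model is the primary one, or only baseline values are used, the mediation problem does not touch the primary result. The documents do not settle which of these applies.

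**What to change.** For Aims 1 and 2:

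- Allow only named, pre-specified covariates measured before randomisation, for example child age and sex, enrolment cycle and community. LAZ is already standardised for age, so age will add little there. Baseline values of pathway constructs are acceptable if named in advance.
- Delete the Fig. 2 rule and the p < .1 rule for these models.
- Choose one treatment of the baseline outcome. Baseline is already one of the five modelled waves, so either keep it as a wave, or use it as a covariate and remove it from the response. It should not be both.

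For Aim 3, reserve the Fig. 2 pathway variables measured after randomisation for the mediation models already planned.

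The cost is wording and one modelling decision on baseline, made before outcome data are examined. Age comes from the date of birth recorded at baseline, and cycle and community follow from the recruitment scheme, so no new data collection should be needed. Moving the baseline outcome to the covariate side would require respecifying the growth curve.

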### Sample size

The study sample will comprise 600 mother-infant dyads, with 200 eligible pairs each assigned to one of the three study conditions. Using the software Optimal Design (Version 3.01) [64], we determined that a sample of 600 participants will lend our study adequate statistical power which allows us to observe an effect from the study interventions. Using the repeated measures module of the software under the setting of a cluster randomized trial with person-level outcomes and assuming an intraclass correlation coefficient (ICC) of 0.7, we found that the study will have a statistical power of 0.80 to detect an effect size of 0.338, which is slightly above the small effect size defined by Cohen’s d. The ICC of 0.7 is typical for individual’s serial correlation found from most longitudinal studies. If the ICC is reduced to 0.3, the study can detect an even smaller effect size of 0.31.

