**Primary outcomes**			
Child growth	Anthropometric measures of height and weight	Length-for-age Z score (LAZ) Weight-for-age Z score (WAZ) Weight-for-length Z score (WLZ)	Baseline, 3 mo, 6 mo, 9mo, 12 mo
Cognitive, Language, Motor and Social Emotional Development	Ages and Stages Questionnaires (ASQ)– Social-Emotional, Communication, Gross Motor, Fine Motor, and Problem-Solving Domains	ASQ scores	Baseline, 6 mo, 12 mo

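### The primary growth curve treats baseline as an outcome wave and states no common baseline mean or baseline adjustment; fitted in the conventional way it stays valid but gives up precision that costs nothing to keep

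*Protocol article*

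**What the plan says.** All of this is in the protocol article.

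- **Model.** Under Statistical analyses (Primary and secondary outcomes), the primary model for aims 1 and 2 is a growth curve fitted by HLM or HGLM. Baseline is one of its waves: "the different timepoints (i.e., five waves of data collection at baseline and 3-, 6-, 9-, and 12-month follow-ups) are nested within children". The structure is given as "we apply a two-level HLM model that treats time as level 1 and children as level 2". The fixed effects are not written out. The text does not say whether each arm has its own intercept, or whether the tested contrast is a slope, a 12-month difference or an average.
- **Covariates.** The same section says that "baseline and endline characteristics for the outcomes of interest will be presented in a table", and then that "Several variables represented in summary statistics will also be used as covariates in adjusted outcome analyses". It adds an empirical rule: "Empirically derived covariates will be included in analyses when a p-value < .1 results from the likelihood ratio test or the Wald test". The baseline value of the outcome is neither named nor excluded.
- **Measurement times.** Table 3 lists growth at "Baseline, 3 mo, 6 mo, 9mo, 12 mo" and the ASQ at baseline, 6 and 12 months.
- **Correlation.** The Sample size section works by "assuming an intraclass correlation coefficient (ICC) of 0.7", described as within-child serial correlation, with 0.3 as an alternative.
- **Allocation.** The Randomization section has the mother pick an envelope during enrollment. The order of that step and the baseline assessment is not given.

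**The concern.** In a conventional two-level growth curve, a child-level factor such as arm predicts both the child's intercept and the child's slope. The arms are then free to differ at baseline, and the treatment effect is estimated net of the observed baseline difference, much as with a change score. Randomisation makes the baseline means equal in expectation, so estimating three of them spends information on differences that can only be chance. A model with one shared baseline mean, or one that adjusts for baseline, uses the same data with a smaller standard error.

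Two matters follow. Hypothesis 3 (0.10 LAZ, Grandi Byen against egg) is the hardest primary hypothesis to detect, so precision matters most there. And the covariate rule, as worded, leaves room for baseline LAZ or ASQ to enter as a covariate while the same value is also a level-1 outcome, which is not a valid adjustment.

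**Working it through.** **Inputs from the article.** 200 children per arm; ICC ρ = 0.7 (main) and 0.3 (alternative); waves at 0, 3, 6, 9, 12 months (LAZ) and 0, 6, 12 months (ASQ); Hypothesis 3 effect 0.10 LAZ; one-sided testing.

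**Assumptions.** Alpha 0.05 (none is stated), unit SD, compound symmetry, linear time scaled so that 12 months = 1, no dropout, effect read at 12 months.

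**The plan's own power figure.** The article gives 80% power for an effect of 0.338 at ICC 0.7 and 0.31 at ICC 0.3. The usual formula, (zα + zβ)·√[4(ρ + (1−ρ)/n)/J], was tried with children as clusters and waves as members.
- J = 400, n = 5, two-sided: 0.244 at ICC 0.7 and 0.186 at ICC 0.3.
- J = 200, n = 5, two-sided: 0.345 and 0.263.
- A search over J = 20 to 600, n = 2 to 40 and several alphas found no combination that gives both stated figures.

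This does not show the figures to be wrong, because the alpha, cluster count, wave count and variance components used are not given. Nothing below depends on them.

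**Variance of the 12-month arm contrast, random intercept only.** The contrast variance is 2v/200, where the per-child term v is:
- Arm-specific baselines: v = (1−ρ)/Sxx, with Sxx = Σt² − (Σt)²/m.
- Common baseline: v = (1−ρ)/[Σt² − ρ(Σt)²/(1 + (m−1)ρ)].

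LAZ: m = 5, Σt² = 1.875, (Σt)² = 6.25, Sxx = 0.625. ASQ: m = 3, Σt² = 1.25, (Σt)² = 2.25, Sxx = 0.5.

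| Outcome | ICC | v, arm-specific | v, common | Ratio | Variance saved |
|---|---|---|---|---|---|
| LAZ | 0.7 | 0.3/0.625 = 0.480 | 0.3/0.7237 = 0.4145 | 0.864 | 13.6% |
| ASQ | 0.7 | 0.3/0.5 = 0.600 | 0.3/0.5938 = 0.505 | 0.842 | 15.8% |
| LAZ | 0.3 | 0.7/0.625 = 1.120 | 0.7/1.0227 = 0.684 | 0.611 | 38.9% |
| ASQ | 0.3 | 0.7/0.5 = 1.400 | 0.7/0.8281 = 0.845 | 0.604 | 39.6% |

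**With a random slope.** An assumed slope variance of 0.2 over 12 months, uncorrelated with the intercept, adds 0.2 to both v terms.
- ICC 0.7: LAZ 0.6145/0.680 = 0.904; ASQ 0.705/0.800 = 0.882. Saved: about 10% and 12%.
- ICC 0.3: LAZ 0.884/1.320 = 0.670; ASQ 1.045/1.600 = 0.653. Saved: about 33% and 35%.

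**Power for Hypothesis 3.** Power = Φ(0.10/SE − 1.645), with SE = √(2v/200).
- ICC 0.7: SE 0.0693 gives 0.42; SE 0.0644 gives 0.46.
- ICC 0.3: SE 0.1058 gives 0.24; SE 0.0827 gives 0.33.
- With the random slope: 0.33 to 0.36 at ICC 0.7, and 0.22 to 0.28 at ICC 0.3.
- Two-sided 0.05 without the random slope: 0.30 to 0.34, and 0.16 to 0.23.

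**Hypotheses 1 and 4.** At ICC 0.7 both are already near 1 under these idealised assumptions. At ICC 0.3, without a random slope, Hypothesis 1 (0.30 LAZ) moves from 0.88 to 0.98 and Hypothesis 4 (0.36, on the ASQ) from 0.92 to 0.99.

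**The case against.** The strongest reply is that the article never says arm has its own intercept. Listing baseline as a wave is equally compatible with a model containing arm-by-time terms only, which loses nothing, and an article may leave such terms to the SAP. This stands in part. A reader might infer that the authors have decided to analyse change scores; the text does not support that, and the loss is conditional on free arm intercepts. What remains is that the article does fix the primary model, baseline's place in it and a covariate rule, and the usual form of that model is the less precise one.

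Four further inferences are tempting and should not be drawn.

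- **That the analysis is biased.** A growth curve with free intercepts is valid under randomisation. The issue is efficiency.
- **That the loss is simply 14-40%.** That range merges two ICCs. At the main ICC of 0.7 it is 14-16%, and less with random slopes, which are usual in growth curves.
- **That the stated 80% power would rise by a calculable amount.** The article's detectable effect falls from 0.338 to 0.31 as the ICC falls, as it does for a mean over waves. A slope contrast goes the other way: at 80% power, one-sided 0.05, the LAZ figure with arm-specific baselines rises from 0.172 to 0.263. The slope ratios therefore cannot be applied to that power figure, which gives no support to a change-score reading.
- **That the same loss applies to biomarkers measured only at baseline and 6 months.** The article assigns this model to the primary hypotheses of aims 1 and 2, not to those outcomes.

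It is also fair to say that a common baseline is justified only if baseline is measured before allocation is known. The article does not give the order, and the ASQ is reported by the mother who draws the envelope. That belongs in the fix.

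**Conclusion.** The point holds as a free improvement, not as an error in the plan. If the growth curve is fitted with arm on both intercept and slope, a common baseline would lower the variance of the arm-by-time contrast by about 14-16% at ICC 0.7 (10-12% with the assumed random slope) and about 39-40% at ICC 0.3 (33-35%). At the main ICC the practical gain is modest: about 4 points of power for Hypothesis 3, or about 2 with the random slope, and almost nothing for Hypotheses 1 and 4. At ICC 0.3 Hypothesis 3 gains about 9 points, or about 6 with the random slope. It stays below 0.5 in every case computed, so this change does not rescue it. The sizes rest on compound symmetry or the assumed slope variance, unit SD, linear time, no dropout and an assumed alpha of 0.05. Double use of baseline as outcome and covariate is something the covariate wording permits, not something the article says will happen.

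**What to change.** In the Statistical analyses section (or the SAP, if it sets out the model terms), for LAZ and the ASQ domains:

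1. State that the primary growth curve constrains the arms to a common baseline mean: baseline stays as the first wave, with arm-by-time terms and no arm main effect at time 0. Alternatively, state that baseline is removed from the outcome vector and entered as a fixed covariate, with arm and arm-by-time terms at the follow-up waves.
2. State that the baseline outcome is not also entered through the covariate rule while it is a level-1 outcome.
3. Name the contrast to be tested.
4. Confirm that baseline measures, especially the parent-reported ASQ, are taken before the envelope is opened. If they are not, the common-baseline constraint needs separate justification.

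The cost is a few sentences and one changed model term. No data, visits or participants are added.
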